#### Intervention B

Face-to-face physiotherapist-led breathing exercises: Unphonated breathing control exercises will be led by a physiotherapist and expert in BPD. Exercises will be performed according to best practice guidance.^1 21 40 41^

### Assessment part of the interventions (Session 1)

Both the physiotherapist-led intervention (Intervention A) and the music therapist-led intervention (Intervention B) include an assessment component from the physiotherapist and music therapist. Participants will return on a separate day within a month following their baseline assessment and receive an initial hour-long, face-to-face, one-to-one assessment and training session by a music therapist or physiotherapist. The therapist will check if nothing major changed in between the time of baseline appointment and screening session, in terms of their functional status, based on self-report. This initial training session will be done in line with contemporary university guidance and regulations in relation to COVID-19, which currently include using well-ventilated spaces and masks worn by assessment staff. Participants will need to take masks off during assessment and intervention. Following the first session, an individualised treatment plan will be recommended and home exercises given accordingly, aligned with the structure of each intervention method. Online supplemental table 1 provides a detailed overview of the two interventions.

10.1136/bmjresp-2022-001414.supp1Supplementary data

### Physiotherapist and music therapist intervention introduction (Session 1)

For both interventions, during this session the focus will be on awareness and self-assessment of breathing pattern followed by the teaching of breathing exercises aimed at altering breathing pattern. Following this, the participants will be encouraged to perform a set of 5 min of home exercises, for 6 weeks, morning and evening every day, with advice and scope for progression or regression of minutes of practice and/or difficulty of tasks. A paper home exercise diary will be provided to the participant regardless of which group they are randomised to. This home exercise diary will be individually tailored according to progress made in the first face-to-face treatment session. This diary will include days of the week, exercises performed and minutes of practice per exercise.

### Refresher and progression follow-up (Session 2)

Each participant will receive one online one-to-one 30-minute follow-up session, 3 weeks after the initial training session (either provided by the music therapist or by the physiotherapist, depending on group allocation). This 30-minute session will offer repeat intervention and re-focus exercises to those which are most beneficial to the participant at that stage (as determined by the therapist) and can be progressed accordingly. Therapists will make notes of these meetings, to record their decision making and justification. We acknowledge that in clinical practice patients are often offered further follow-ups with progression to assessment of BPD during exercise. However, due to funding limitations for this pilot study, further assessments will not be possible. Evidence suggests that the majority of people with BPD do not require repeated follow-ups to gain significant clinical benefit.^1 42^

### Similarity of interventions

The interventions will be similar in terms of the dose provided and contact time with the respective therapist. However, the music therapist-led exercises will be predominantly phonated, whereas the physiotherapist-led breathing exercises will be unphonated. Both interventions may use bio-feedback, visualisation, relaxation-oriented strategies and counting strategies. The toolbox of options for therapy is standardised per intervention, but not every participant will receive all possible exercises. Therapists will record which exercises are given to each participant. The intervention will be individually tailored for the patient, which is common clinical practice. This also reflects other areas of exercise-based modalities, such as pulmonary rehabilitation, whereby a fixed set of possible exercises is available to choose from, but *what* exercise is chosen, and *how* that exercise is performed are individually tailored based on clinical judgement.^43^

### Follow-up assessment

Participants will be asked to return to Brunel University London, within a 2-week timeframe following their final week performing the intervention (so either in week 6 or week 7), to repeat all the measurements included at the screening assessment. Adverse events will also be recorded. Home exercise diaries will be collected during this assessment. As such, there are four participant contact points in total: (1) baseline screening/assessment; (2) training session 1, in week 1; (3) intermediate refresher session in week 3; (4) follow-up assessment in week 6 (or week 7). As stated earlier, the assessment will be performed by a blinded assessor.

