## Recruitment

### Online screening

Participants who register their interest to participate in the study will be sent an email asking them to complete the NQ,^10^ a patient-reported outcome measure that assesses functional respiratory complaints.^1 24^ The NQ has become the standard outcome measure used to identify BPD. Only participants who score at least 19 at screening^1 18^ will continue onto the study and repeat the questionnaire at their baseline assessment and post therapy.

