#### Primary outcome

Between-group differences in change of NQ score post intervention (mean, SD, CIs and effect size).

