#### Secondary outcomes

##### Feasibility

Number of individuals completing both arms of the RCT study. At least 66% completion will support using that intervention in a future definitive randomised controlled study. The study team determined that below a 66% completion rate would either indicate significant changes to the study design are required prior to performing a definitive trial, or that a further definitive study is not feasible depending on other outcome analysis.Percentage of individuals recruited from screening, according to use of Nijmegen and BPAT screening tool.Perceived participant experiences of interventions and the feasibility of the study design, collected via semistructured interview.

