### Safety reporting

Adverse events will be recorded and followed up until resolved.

Individuals who return a positive lateral flow test and subsequent PCR test at any stage after consent to the study will be withdrawn from continuing in the study due to the known respiratory complications arising from COVID-19.^47^

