### Discontinuation

All participants are free to withdraw at any time from either intervention. Reasons for withdrawal will be collected and timing will be recorded because this information will help plan for the future definitive study. Withdrawn subjects will not be replaced on the trial.

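### The only stated route to the post-treatment NQ is a campus visit, so the primary outcome is lost by rule for COVID-positive participants and may be lost for others who stop or do not attend

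*Protocol article*

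**What the plan says.** All references are to the protocol article.

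- **Outcome.** The Primary outcome section defines it as the between-group difference in change of NQ. The Abstract words it as the post-intervention difference. Either needs a post-treatment NQ.
- **Instrument.** Online screening describes NQ as "a patient-reported outcome measure that assesses functional respiratory complaints". People who register interest "will be sent an email asking them to complete the NQ".
- **Post-treatment route.** Under Follow-up assessment: "Participants will be asked to return to Brunel University London, within a 2-week timeframe following their final week performing the intervention". All screening measurements are repeated there. The section then counts four participant contact points in total, and this visit is the only one after treatment.
- **COVID-19.** Under Safety reporting, anyone with a positive lateral flow test and then a positive PCR at any stage after consent "will be withdrawn from continuing in the study".
- **Stopping.** Under Discontinuation: "All participants are free to withdraw at any time from either intervention". Reasons and timing are collected, and withdrawn participants are not replaced. The section does not say whether NQ is still sought.
- **Non-completers.** The Qualitative study section defines them by a missed half-way session and/or less than two thirds of the recommended exercise sessions. It plans remote interviews of 30 to 60 minutes with up to seven of them.
- **Progression.** Under Feasibility: "At least 66% completion will support using that intervention in a future definitive randomised controlled study".
- **Analysis.** Statistical analyses specifies a group-by-time repeated measures ANOVA for 40 participants randomised 1:1. The NQ results also feed the sample size for the definitive trial.

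**The concern.** A short self-completed questionnaire is the primary outcome, and the trial can already obtain it remotely. Tying its only post-treatment collection to travel means that anyone who does not make the visit has no primary outcome. The trial is prepared to reach people who stopped the exercises for a long remote interview, yet names no remote route for the questionnaire itself.

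Two things are at stake. The first is validity: if people who see little benefit are less likely to return, and more so in one arm, the comparison among attenders no longer estimates the randomised comparison. The second is precision, which is already limited with 20 per arm. Both carry forward, because the definitive trial is to be sized from these NQ results. The recovery (NQ below 17) and 10-point responder percentages depend on the same measurement.

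**Working it through.** **1. Who has a stated route to the post-treatment NQ?**

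| Group after randomisation | What the article says | Post-treatment NQ |
|---|---|---|
| Attends the visit | All measurements repeated | Obtained |
| Low adherence, not withdrawn | Still among the participants asked to return | Obtained if they attend |
| Stops the intervention voluntarily | Reasons and timing collected; follow-up not mentioned | Unclear |
| Does not attend | No alternative stated | None |
| COVID-positive as defined | Withdrawn from the study | None, by rule |

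The COVID-19 rule can act for some time after randomisation. Session 1 may fall up to a month after baseline (about 4 weeks), and follow-up is in week 6 or 7, so the exposure can reach about 10 to 11 weeks. The article gives no infection rate, so the number affected is unknown.

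**2. What the analysis does with a missing value.** With two timepoints, the group-by-time term of a standard repeated measures ANOVA is the comparison of change scores. A person without the second NQ has no change score and drops out.

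**3. Precision.** The article's figure is 40 in total. It comes with no numerical effect size, SD or dropout rate, so it can be neither reproduced nor refuted, and nothing here shows it to be wrong.

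- 66% of 40 is 26.4, or about 26. With equal arms, the standard-error ratio to full data is sqrt(40/26) = 1.24.
- Per arm, 66% of 20 is 13.2, so 14 is the smallest whole number that meets the threshold. Then sqrt(40/28) = 1.20.
- The 95% CI half-width, in SDs of NQ change, is t(0.975, 2n − 2) × sqrt(2/n). It is 0.64 for n = 20 per arm, 0.72 for n = 16, 0.78 for n = 14 and 0.81 for n = 13. The last two are 21% and 26% wider than full data.
- If, as an assumption, half of 14 missing participants answered by email, 33 of 40 would have NQ and the ratio would be sqrt(40/33) = 1.10.

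These figures treat everyone who does not complete as having no NQ. That is the upper end of loss for a trial at the threshold, not a forecast.

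**4. Bias, by assumption only.** Suppose those lost improve g points less than those seen, with a fraction p lost in an arm. The full-arm mean change is then p × g below the attenders' mean, so the attenders-only difference between arms is off by g × (p1 − p2).

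- With g = 5 NQ points and losses of 34% v 20%: 5 × 0.14 = 0.7 points.
- With g = 5 and losses of 34% v 10%: 5 × 0.24 = 1.2 points.
- In SD units, with g from 0.5 to 1.0 SD: 0.05 to 0.10 SD at 20% v 10%, and 0.12 to 0.24 SD at 34% v 10%.
- With equal loss in both arms and the same g, the bias is zero.

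The precision and bias scenarios are therefore different cases. At 34% v 10% (13.2 and 18 per arm) the standard-error ratio is sqrt[(1/13.2 + 1/18)/(2/20)] = 1.15. At 34% v 20% (13.2 and 16) it is 1.18.

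**The case against.** A reader might infer that NQ is lost for non-completers, or that stopping the exercises means leaving the trial. The article does not support either. Non-completion is defined by adherence and only for the interviews, and the return visit is asked of participants without condition. Paper diaries are collected at that visit, so low adherers are evidently expected there. Discontinuation speaks of withdrawing from the intervention and does not say that follow-up ends. Withdrawal from the study is explicit only in the COVID-19 rule.

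Nor is 66% a rate of missing NQ. It is a completion threshold for progression, and someone who stops exercising but attends still has an outcome.

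A further objection is that a condensed article may leave data collection after withdrawal, and missing-data rules, to a fuller protocol or SAP. That stands for what happens after voluntary withdrawal. It does not remove the point, because the article itself states a closed list of contacts with one post-treatment assessment on campus, and a rule that takes COVID-positive participants out of the study.

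On-site collection in a fixed order, matching baseline, is also a defensible choice. Emailing only non-attenders mixes modes within a change score and ties mode to non-attendance. Dropping emailed responses then returns the attenders-only result, so it cannot correct a mode effect. This is a real limitation of the remedy. Still, showing both results tells the reader more than the attenders-only result alone.

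Finally, the assumed bias of 0.7 to 1.2 points is small beside the 10-point change that the protocol calls clinically relevant, and beside a half-width of 0.64 SD with full data. The 10 points refer to change within a person, however, and the Introduction says that NQ has no established minimal important difference for comparing interventions.

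**Conclusion.** The point holds in limited form. The visit-only route is stated, the questionnaire does not need a visit, and the COVID-19 rule removes the primary outcome for those it affects. For people who stop the intervention or do not attend, loss is a risk and not a stated rule.

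The size is unknown. A standard-error ratio of 1.24 applies only if completion is at about 66% and no non-completer supplies NQ. Smaller losses cost less. The bias range rests wholly on assumed gaps in improvement and assumed differences in loss between arms. At its top (0.24 SD) it slightly exceeds a conventionally small effect (assumed d = 0.2), which is relevant because the plan expects a small effect without giving a number.

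This does not invalidate the pilot or its sample size. It is an avoidable risk to the primary outcome that should be corrected because the correction is cheap.

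**What to change.** - **Follow-up assessment and Discontinuation.** State that stopping the intervention does not end outcome collection. In the follow-up window, email NQ and Breathe-VQ to every randomised participant who does not attend and has not withdrawn consent for data. BPAT and spirometry stay on site.
- **Analysis.** Include these responses under the allocated arm, record the mode (visit or email), and report the primary analysis with and without emailed responses.
- **Safety reporting.** Leave the rule on stopping treatment after a positive test unchanged; it is a clinical matter and is not judged here. Seek the emailed NQ where the participant agrees, record COVID-19 status, and show results with and without these participants.

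**Cost.** A minor amendment and a few emails through a route already in use, with no added visit. The price is a possible difference between emailed and on-site NQ, which the with-and-without comparison makes visible but cannot remove.

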### Qualitative study

Semistructured one-to-one interviews with a purposive sample of 21 participants will be performed in order to explore their perceptions of participating in the trial. We aim to recruit seven people randomised to the music therapist-led led breathing exercises, seven people randomised to the physiotherapist-led breathing exercises and (up to) seven non-completers of the interventions, defined as participants who did not participate in the half-way online meeting and/or who completed less than two thirds of the recommended exercise sessions (4 out of 6 weeks’ equivalent sessions). Interviews (and analysis) will be led by AL, who has extensive experience with qualitative research in the context of respiratory physiotherapy and will be completed via MS Teams. The topic guide (see appendices) includes questions about experiences of trial participation, attitudes towards content, delivery and timing of the intervention, and suggestions for improvements (both regarding the interventions as well as the larger study). It is expected that the qualitative interviews will last between 30 and 60 min. All interviews will be recorded using a Philips digital Dictaphone or MS Teams. Digital files will be uploaded to a secure online data repository, OneDrive, which all study team members involved in the analysis will have access to.

#### Primary outcome

Between-group differences in change of NQ score post intervention (mean, SD, CIs and effect size).

#### Secondary outcomes

##### Feasibility

Number of individuals completing both arms of the RCT study. At least 66% completion will support using that intervention in a future definitive randomised controlled study. The study team determined that below a 66% completion rate would either indicate significant changes to the study design are required prior to performing a definitive trial, or that a further definitive study is not feasible depending on other outcome analysis.Percentage of individuals recruited from screening, according to use of Nijmegen and BPAT screening tool.Perceived participant experiences of interventions and the feasibility of the study design, collected via semistructured interview.

##### Insight into effect of interventions

Percentage of participants in each arm who are deemed recovered post-therapy (less than 17) and therefore no longer diagnosed with BPD.^41^Percentage of participants in each arm who demonstrate clinically relevant change in the NQ (at least 10 points).^41^Between-group differences in Breathe-VQ questionnaire.Between-group differences in BPAT scores.

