## Methods and analysis

### Population

We aim to recruit 40 young adults aged between 18 and 40 years who have BPD, using Brunel University London Research Participation website, posters placed around campus and via investigator and Brunel University affiliated social media accounts. This sample size is in line with previously recommended ranges for pilot and feasibility designs.^34 35^ This is an assessor blinded 1:1 randomised controlled trial (RCT) pilot study with qualitative interview substudy.

Inclusion criteria are as follows:

Young adults between 18 and 40 years with a score of at least 4 on the BPAT^11^ or at least 19 on the NQ.^18^ BPDs are common in younger populations^12^ and we want to optimise the interventions based on findings in this study before testing in potentially more frail populations. Both outcomes will be used as there is no single gold standard diagnosis for BPD.Access to an internet-enabled device.Normal spirometry according to forced expiratory volume in the first second (FEV_1_) and forced vital capacity (FVC) above 80% of that predicted for age, height, sex and race.

Exclusion criteria are as follows:

Previously received one-to-one singing tuition or physiotherapy led breathing control exercises.Previously or currently member of a choir.Diagnosis of other respiratory diseases which may lead to BPD (i.e., Asthma, COPD, long COVID, Bronchiectasis, Interstitial Lung Disease, chronic cough, sinus disease).Diagnosis of neurological disease which impacts on respiratory system.Unable to provide consent.Pregnant

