### Face-to-face baseline/screening assessment

Assessments will be performed by an individual who has received training in breathing pattern assessment. The assessment will include the following:

Medical history, medication history, social history and demographic information such as age, sex, height and weight will be recorded. Next, screening and baseline spirometry will be performed using a portable spirometer (Micromedical Microlab 3500 Mk8) according to international guidelines.^36^ Should any abnormal finding become present following the spirometry, that is, FEV_1_ or FVC under 80% predicted, repeat spirometry may be indicated. Should abnormal findings be repeated individuals, will not continue into the study and the participant will be encouraged to contact their General Practitioner.

The participant will then complete the following outcomes:

The Nijmegen Questionnaire as described above.

The Breathing Hypervigilance Questionnaire (Breathe-VQ) is a six-question Likert scale response questionnaire. It has been developed by the current study team and has shown to have good construct validity, internal consistency and test-retest reliability in a study comprising of young dysfunctional breathers and non-dysfunctional breathers.^37^ The Breathe-VQ screens for the presence of excessive anxious, conscious monitoring of breathing state (‘hypervigilance’), which is thought to potentially contribute to the experience of breathlessness.^38^ Our hypothesis is that the interventions could also indirectly help to improve breathing pattern by reducing such vigilance and awareness. The Breathe-VQ will be used as a secondary outcome measure exploring its responsiveness to change post intervention for the first time.

The Breathing Pattern Assessment Tool: This is a clinician-led assessment of BPD.^11^ The clinician scores between 0 and 2 for different areas of assessing breathing pattern, including abdominal/chest movement, inspiratory flow, expiratory flow, channel of inspiration (nose or mouth), air hunger, respiratory rate and rhythm. The higher the score, the worse the breathing pattern. A score of at least 4 indicates BPD. Individuals will be asked which time of year their breathing is worse, and if there are any significant triggers for their BPD.

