Participants who score at least 19 on the NQ or 4 on the BPAT will continue onto the study. Participants who do not record a score of at least 19 on the NQ or 4 on the BPAT will be excluded from the study at this stage. This information will be important to plan for a future definitive study. Participants will complete the Breathe-VQ, followed by the NQ, and a trained research assistant will then perform a BPAT in that order.

In total, the baseline screening/assessment will last approximately 1 hour.

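### The recovery outcome removes the BPD diagnosis on the NQ alone and sets no baseline condition, so each arm's recovery percentage can be overstated

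*Protocol article*

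**What the plan says.** The protocol article, under Insight into effect of interventions, lists the "Percentage of participants in each arm who are deemed recovered post-therapy (less than 17) and therefore no longer diagnosed with BPD". It attaches no condition on the baseline score and none on the BPAT.

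Entry is defined on two instruments. The inclusion criteria under Population accept either a BPAT of at least 4 or an NQ of at least 19, and explain: "Both outcomes will be used as there is no single gold standard diagnosis for BPD". The face-to-face baseline section repeats the either/or rule: "Participants who score at least 19 on the NQ or 4 on the BPAT will continue onto the study". On the BPAT it states: "A score of at least 4 indicates BPD".

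Before that visit there is an online NQ screen: "Only participants who score at least 19 at screening" go forward. The abstract also gives only the NQ threshold. The NQ is then completed again at baseline and after therapy, and the Follow-up assessment section has every screening measurement repeated, which includes the BPAT.

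**The concern.** The diagnosis is made with either of two instruments but removed with one. Two kinds of participant are then labelled in a way that the protocol's own criteria contradict:

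- someone whose follow-up NQ is below 17 but whose BPAT is still 4 or more;
- someone retained at baseline on the BPAT with an NQ already below 17, who counts as recovered with no change at all.

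This matters mainly for each arm's absolute percentage. Both arms are active and there is no untreated group, so a recovery percentage is likely to be read as evidence that a therapy works. The article's summary box anticipates a role in treatment guidelines if both therapies are judged effective.

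**Working it through.** The protocol gives no expected recovery rate, NQ mean or SD, reliability, or share of BPAT-positive people, so there is no planned figure to reproduce.

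**1. Which score is meant.** The BPAT section says "The clinician scores between 0 and 2 for different areas of assessing breathing pattern" and lists seven areas. The maximum over those areas is 7 × 2 = 14. A cut-off of 17 cannot be a BPAT score, so it is the NQ.

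**2. The diagnostic label.** Take follow-up NQ 16 and BPAT 5. Recovery rule: 16 < 17, so recovered and no longer diagnosed. Entry rule: 5 ≥ 4, so BPD is indicated. The two statements conflict, and no assumption is needed to show it.

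**3. The baseline route.** A person scores NQ 19 or more online, then below 17 at the baseline visit, with BPAT 4 or more. The baseline rule keeps this person. If nothing changes afterwards, the outcome counts a recovery. The online screen narrows this route, because the NQ must first fall from at least 19 to below 17 without treatment, but does not close it.

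**4. Size per person.** 40 participants at 1:1 give 20 per arm. With k such people in an arm and nobody changing, recovery is k/20: 1 gives 5%, 2 give 10%, 4 give 20%.

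**5. Size under assumptions.** Simulation with no treatment effect, 2,000,000 registrants per scenario. Assumed, not from the protocol: NQ mean 18 or 24, SD 9, retest reliability 0.7 or 0.9, scores rounded and held within 0 to 64; BPAT of at least 4 in 30% or 60% of registrants, BPAT reliability 0.7, correlation 0.3 between the underlying NQ and BPAT values. Entry: online NQ ≥ 19, then baseline NQ ≥ 19 or BPAT ≥ 4. Results are percentages of entrants, except that column C is a percentage of those with baseline NQ ≥ 19.

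| NQ mean | Reliability | BPAT ≥ 4 | A: baseline NQ < 17 | B: recovered as written | C: recovered, baseline NQ ≥ 19 | B − C |
|---|---|---|---|---|---|---|
| 18 | 0.7 | 30% | 6.5 | 13.3 | 11.0 | 2.3 |
| 18 | 0.7 | 60% | 12.1 | 15.5 | 10.9 | 4.6 |
| 18 | 0.9 | 30% | 2.5 | 4.7 | 3.5 | 1.2 |
| 18 | 0.9 | 60% | 4.8 | 5.9 | 3.5 | 2.4 |
| 24 | 0.7 | 30% | 2.4 | 6.5 | 5.7 | 0.8 |
| 24 | 0.7 | 60% | 5.2 | 7.5 | 5.7 | 1.8 |
| 24 | 0.9 | 30% | 0.9 | 2.3 | 1.8 | 0.5 |
| 24 | 0.9 | 60% | 2.1 | 2.9 | 1.8 | 1.1 |

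The missing baseline condition therefore adds 0.5 to 4.6 points. Most of column B is regression to the mean, which remains in column C.

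Among those counted in column B, 31% to 69% still have BPAT ≥ 4 at follow-up. As a share of all entrants that runs from 2.3% × 0.319 = 0.7% to 15.5% × 0.691 = 10.7%. This overlaps with the baseline route, so the two are not to be added.

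With both corrections (baseline NQ ≥ 19, and follow-up NQ < 17 with BPAT < 4), null recovery is 0.8% to 7.5%.

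**6. Sensitivity.** If the either/or rule applied without the online screen, 5% to 30% would enter with NQ < 17 and 8% to 35% would be recovered under no effect. A second set of assumptions keeps the online screen: 22% of registrants with NQ ≥ 19, SD 6 to 10, reliability 0.7 to 0.9, BPAT positive in half independently of the NQ. It gives 6.2% to 26.6% as written against 3.3% to 18.9% with baseline NQ ≥ 19. The range ends differ by 6.2 − 3.3 = 2.9 and 26.6 − 18.9 = 7.7 points.

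**7. Between arms.** The rule is the same in both arms and allocation is random after baseline, so the expected difference under no effect is 0. The chance standard error is √(2p(1 − p)/20): 9.5 points at p = 0.1 and 15.5 at p = 0.4.

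**The case against.** The strongest reply is the online screen. With NQ of at least 19 required before the visit, a low baseline NQ needs an untreated fall, and the share affected is small. This stands as a limit on size: column A is 1% to 12%, not the 5% to 30% obtained without the screen. It does not answer the label problem, which concerns the BPAT at follow-up.

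It can also be said that the online screening section treats the NQ as the standard instrument, and that the cut-off of 17 comes from a cited source. Neither the cut-off nor reporting an NQ percentage is in dispute. What does not follow is the step from NQ below 17 to absence of the diagnosis, given the stated lack of a single gold standard.

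Detail on intervals and denominators often belongs in a statistical analysis plan, which is not shown, so none is asked for beyond the definition. But the definition itself is stated here, and it conflicts with the entry rule.

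Two stronger readings are tempting and are not supported:

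- *The comparison between arms is biased.* One or two low-NQ entrants in one arm would move it by 5 to 10 points, but that is chance imbalance, within the standard error above. Randomisation makes the inflation equal in expectation; the cost is noise and possible dilution of a real difference.
- *The companion outcome, an NQ change of at least 10 points, counts worsening, and people entering below 10 can never reach it.* These two claims exclude each other. The item sits among effects of the interventions and is described as clinically relevant, so improvement is the natural reading.

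**Conclusion.** The concern holds in limited form. The contradiction between the recovery label and the entry criterion follows from the text alone. The baseline route also follows from the text. Its size depends on assumed NQ spread, reliability and BPAT prevalence: with the online screen, about 0.5 to 4.6 points in the main set of scenarios and roughly 3 to 8 in the second.

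The effect is on each arm's absolute percentage. A reader might infer that the trial's main conclusions are at risk, but the documents do not support that. The primary outcome is change in NQ, the future sample size uses the primary NQ results with screening, recruitment and drop-out rates, and the only numerical progression threshold is 66% completion. None of these uses the recovery outcome. For a descriptive secondary outcome in a pilot, severity is minor to moderate.

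**What to change.** Change the outcome definition in two sentences:

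1. Report the percentage with follow-up NQ below 17 only among participants whose baseline NQ was at least 17 (or at least 19, to match the entry cut-off), and show by arm how many entered below that value. A floor of 17 removes only those already under the cut-off; 19 also drops entrants at 17 or 18, who can genuinely cross it. The restriction uses a score taken before randomisation, so the arms stay comparable.
2. Either reserve the statement that BPD is no longer diagnosed for NQ below 17 together with BPAT below 4 at follow-up, or drop that statement and name the outcome simply as NQ below 17.

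The abstract and the online screening section (NQ required) should also be reconciled with the inclusion criteria and the baseline section (either tool suffices), since the size of the baseline route depends on which applies.

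The cost is a slightly smaller denominator and less favourable percentages. No new measurement is needed, because the BPAT is already repeated at follow-up. The change does not remove regression to the mean: about 2% to 11% would still be below 17 under no effect among those with baseline NQ of at least 19 in the main simulation (3% to 19% in the second), so the percentages should not be read as effects of treatment.
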